### **11.6. Regulatory and Ethical Approval**

#### **11.6.1. Ethical and Trust Management Approval**

The Trial has a favourable ethical opinion from a Multi-centre Research Ethics Committee, determining that the trial design respects the rights, safety and wellbeing of the participants.

The Local Comprehensive Research Network will conduct governance checks and assess the facilities and resources needed to run the trial, in order to give host site permission. The Trial Office is able to help the local Principal Investigator in the process of the site specific assessment by completing much of Site Specific Information section of the standard IRAS form as possible. The local Principal Investigator will be responsible for liaison with the Trust management with respect to locality issues and obtaining the necessary signatures at their Trust.

As soon as Trust approval has been obtained, the Trial Office will send a folder containing all trial materials to the local Principal Investigator. Potential trial participants can then start to be approached.

#### **11.6.2. Clinical Trial Authorisation**

The Chief Investigator has obtained Clinical Trials Authorisation from the Medicines and Healthcare Regulatory Authority.

### **11.7. Funding and Cost implications**

The research costs of the trial are funded by a grant from the Medical Research Council awarded to the University of Birmingham. Research midwives employed by the research grant will be available to support the trial in most centres.

Additional costs service support costs associated with the trial, e.g. gaining consent, aliquoting extra blood samples etc, are estimated in the Site Specific Information section of the standard IRAS form. These costs should be met by accessing the Trust's Support for Science budget via the Local Comprehensive Research Network.

### **11.8. Indemnity**

University College London holds insurance to cover participants for injury caused by their participation in the clinical trial. Participants may be able to claim compensation if they can prove that UCL has been

negligent. However, as this clinical trial is being carried out in a hospital, the hospital continues to have a duty of care to the participant of the clinical trial. University College London does not accept liability for any breach in the hospital's duty of care, or any negligence on the part of hospital employees. This applies whether the hospital is an NHS Trust or not.

Participants may also be able to claim compensation for injury caused by participation in this clinical trial without the need to prove negligence on the part of University College London or another party. Participants who sustain injury and wish to make a claim for compensation should do so in writing in the first instance to the Chief Investigator, who will pass the claim to the Sponsor's Insurers, via the Sponsor's office.

Hospitals selected to participate in this clinical trial shall provide clinical negligence insurance cover for harm caused by their employees and a copy of the relevant insurance policy or summary shall be provided to University College London, upon request.

### **11.9. Publication**

A meeting will be held after the end of the trial to allow discussion of the main results among the collaborators prior to publication. The success of the trial depends entirely on the wholehearted collaboration of a large number of doctors, nurses and others. For this reason, chief credit for the main results will be given not to the committees or central organisers but to all those who have collaborated in the trial. A writing committee will be convened to produce publications on behalf of the StAmP Collaborating Group. Centres will not be permitted to publish data obtained from participants in the StAmP Trial that use trial outcome measures without discussion with the Chief Investigator and/or the TSC.

### **11.10. Ancillary studies**

#### **11.10.1. Linkage with the PREP Study**

The data on clinical information including history, examination, clinical findings, laboratory and ultrasound results and clinical outcomes will be shared with the HTA funded study PREP (Prediction of Risks in Early Onset Pre eclampsia). The PREP study aims to develop a prediction model to accurately identify the women with early onset pre eclampsia at risk of adverse maternal and fetal outcomes. The tests are routinely performed as part of standard care in units based on NICE recommendations.

#### **11.10.2. Linkage with other ancillary studies**

It is requested that any proposals for formal additional studies of the effects of the trial treatments on some patients (e.g. special investigations in selected hospitals) be referred to the Trial Management Committee for consideration. In general, it would be preferable for the trial to be kept as simple as possible, and add-on studies will need to be fully justified.

## APPENDIX C: GP LETTER

*To be printed on Local Trust Headed Paper*

*Doctor*  
*Practice*  
*Street*  
*City*  
*Postcode*

*Date*

Dear Dr <gp name>

Name.....D.o.B.....NHS No.....

Your patient, named above, has been diagnosed with severe pre-eclampsia, and is suitable for entry to StAmP, a proof of principle double-blind, randomised placebo-controlled trial of pravastatin to ameliorate early onset pre-eclampsia.

University College London is acting as trial sponsor. The University of Birmingham Clinical Trials Unit are acting as coordinating centre. The study is funded principally by the Medical Research Council. The trial has been approved by the Medicines and Healthcare Products Regulatory Authority (MHRA), a Multicentre Research Ethics Committee and approvals have been obtained at each participating centre.

Your patient has been informed about the **StAmP** trial, has consented to take part and has been randomly allocated to either Pravastatin or Placebo. Both the participant and all clinicians responsible for her care remain blind to their treatment.

If you have any queries about the patient's management, please feel free to contact me. If you require any further information about the **StAmP** trial, it can be obtained from the **StAmP** trial office (see address below). Please file this letter in the patient's notes. I would appreciate being notified if they are no longer one of your patients.

Yours sincerely

*Name*

*Position*

StAmP Trial Office, [name]

[contact]; [contact]; Email: [[contact]](mailto:[contact]); Website: [www.stamp.bham.ac.uk](http://www.stamp.bham.ac.uk)

## APPENDIX D: PRAVASTATIN - EXPECTED TOXICITIES

Toxicities/side-effects that have previously occurred and are listed in the pravastatin SMPC do not have to be reported to the MHRA. If the outcome of the side-effect is serious, the SAE form should be completed. Any SAE not described below, i.e. a serious toxicity that is unexpected, and believed to be related to study treatment, will be reported as a SUSAR (see section 7 of the protocol).

Pravastatin has been studied at 40mg in seven randomised double-blind placebo-controlled trials involving over 21,000 patients treated with pravastatin (n = 10764) or placebo (n = 10719). The following adverse drug reactions were reported; none of them occurred at a rate in excess of 0.3% in the pravastatin group compared to the placebo group.

The frequencies of adverse events are ranked according to the following: very common ( $\geq 1/10$ ); common ( $\geq 1/100, < 1/10$ ); uncommon ( $\geq 1/1,000, < 1/100$ ); rare ( $\geq 1/10,000, < 1/1,000$ ); very rare ( $< 1/10,000$ ).

Nervous system disorders: Uncommon: dizziness, headache, sleep disturbance, insomnia

Eye disorders: Uncommon: vision disturbance (including blurred vision and diplopia)

Gastrointestinal disorders: Uncommon: dyspepsia/heartburn, abdominal pain, nausea/vomiting, constipation, diarrhoea, flatulence

Skin and subcutaneous tissue disorders: Uncommon: pruritus, rash, urticaria, scalp/hair abnormality (including alopecia)

Renal and urinary disorders: Uncommon: abnormal urination (including dysuria, frequency, nocturia)

Reproductive system and breast disorders: Uncommon: sexual dysfunction

General disorders: Uncommon: fatigue

Events of special clinical interest:

Skeletal muscle: effects on the skeletal muscle, e.g. musculoskeletal pain including arthralgia, muscle cramps, myalgia, muscle weakness and elevated CK levels have been reported in clinical trials. The rate of myalgia (1.4% pravastatin vs 1.4% placebo) and muscle weakness (0.1% pravastatin vs < 0.1% placebo) and the incidence of CK level  $> 3 \times \text{ULN}$  and  $> 10 \times \text{ULN}$  in CARE, WOSCOPS and LIPID was similar to placebo (1.6% pravastatin vs 1.6% placebo and 1.0% pravastatin vs 1.0% placebo, respectively).

Liver effects: elevations of serum transaminases have been reported. In the three long-term, placebo-controlled clinical trials CARE, WOSCOPS and LIPID, marked abnormalities of ALT and AST  $> 3 \times \text{ULN}$  occurred at similar frequency ( $\leq 1.2\%$ ) in both treatment groups.

In addition to the above the following adverse events have been reported during post marketing experience of pravastatin:

Nervous system disorders: Very rare: peripheral polyneuropathy, in particular if used for long period of time, paresthesia

Immune system disorders: Very rare: hypersensitivity reactions: anaphylaxis, angioedema, lupus erythematosus-like syndrome

Gastrointestinal disorders: Very rare: pancreatitis

Hepatobiliary disorders: Very rare: jaundice, hepatitis, fulminant hepatic necrosis

Musculoskeletal and connective tissue disorders: Very rare: rhabdomyolysis, which can be associated with acute renal failure secondary to myoglobinuria, myopathy, myositis, polymyositis

Isolated cases of tendon disorders, sometimes complicated by rupture

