### **Expected SAEs**

Expected SAEs are those listed in the current Summary of Product Characteristics (SmPC) for Pravastatin. These events do not meet the criteria of SUSAR unless for reason of their severity. For convenience, the

current expected events for Pravastatin are listed in Appendix D. We will however always use the most recently updated Summary of Product Characteristics (SmPC). The BCTU will ensure that any SmPC updates are circulated to all investigators; in addition, up-to-date SmPCs of licensed products are available at <http://emc.medicines.org.uk/>.

Expected SAEs also include, but are not limited to, the following:

- Symptoms and recognised complications of pre-eclampsia. These include exacerbation of hypertension, abnormal renal function, abnormal hepatic function, disseminated intravascular coagulation, cerebrovascular event, eclampsia, left ventricular failure, haemorrhage and pulmonary oedema.
- Symptoms and recognised complications of premature birth. These include seizures, necrotising enterocolitis (NEC), hypoglycaemia, jaundice, bleeding from umbilicus, and congenital anomalies.

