### **Suspected unexpected serious adverse reactions (SUSARs)**

A SUSAR is an SAE suspected to be related to a product, which is of a **type or severity** which is NOT consistent with the up-to-date product information (i.e. SmPC).

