The BCTU will report all SAEs to the DMEC approximately 3-monthly. The DMEC will view data blinded to treatment but will be able to review unblinded data if necessary. BCTU will also report all SAEs to the main REC and MHRA annually, and to the Trial Steering Committee 6-monthly. The main REC, MHRA and TSC will only view data blinded to trial treatment. Local Investigators are responsible for reporting SAEs to their host institution, according to local regulations, but they do not need to inform MHRA or main REC as this will be done by the BCTU as detailed above.

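### Appendix D's MHRA exemption and type-only SUSAR test conflict with section 7, so an unusually severe listed reaction could miss expedited reporting

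*Combined protocol and SAP*

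**What the plan says.** **Appendix D (Pravastatin – Expected toxicities)** opens with three rules.

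- Listed toxicities and the MHRA: "Toxicities/side-effects that have previously occurred and are listed in the pravastatin SMPC do not have to be reported to the MHRA".
- Serious outcomes: "If the outcome of the side-effect is serious, the SAE form should be completed".
- SUSAR status: "Any SAE not described below, i.e. a serious toxicity that is unexpected, and believed to be related to study treatment, will be reported". The report meant is the SUSAR report, and the sentence ends with a cross-reference to section 7.

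**Section 7.1, Expected SAEs**, says of events in the SmPC: "These events do not meet the criteria of SUSAR unless for reason of their severity". It offers Appendix D for convenience and makes the latest SmPC the reference.

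**Section 7.1, SUSARs**, defines a SUSAR as a suspected related SAE whose type or severity does not fit the up-to-date SmPC.

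**Section 7.3** requires an SAE form for every SAE, faxed to the trials unit (BCTU) within 24 hours, with expectedness judged against the most recent SmPC. On onward reporting it says "BCTU will also report all SAEs to the main REC and MHRA annually". It also sends all SAEs to the DMEC about every 3 months.

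**Section 7.4** starts expedited reporting (7 days if fatal or life-threatening, otherwise 15) from the local investigator's judgement that an SAE is both related and unexpected.

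**The concern.** The protocol gives two rules for when a related serious reaction is unexpected. Section 7 asks about type and severity. Appendix D asks only whether the event is on the list, and equates being unexpected with being unlisted. Its first sentence also exempts listed toxicities from MHRA reporting without qualification, although section 7.3 includes all SAEs in the annual report.

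Severity matters in this trial. The introduction to section 7 notes that the licensing trials excluded pregnant women and that metabolic changes in pregnancy may alter the drug's toxicity in ways that cannot be anticipated. A known reaction in an unusually severe form is one way this could show itself, and Appendix D's test does not allow for it. Two sites could also classify the same event differently, depending on which page they used.

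**Working it through.** No figure in the plan bears on this point, so the check sets the clauses side by side and then follows one event through both.

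**Clauses compared**

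| Question | Section 7 | Appendix D | Result |
|---|---|---|---|
| Can a listed reaction be a SUSAR because of its severity? | Yes (7.1, in two places) | No provision; the test is whether the list describes it | Conflict |
| Do listed serious reactions go to the MHRA? | Yes, annually, with all other SAEs (7.3) | Not required; no limit to expedited reports | Literal conflict |
| Which reference decides expectedness? | Latest SmPC (7.1, 7.3) | SmPC in the first sentence, printed list in the third, then a pointer to section 7 | Partial conflict only |
| Is a serious listed reaction recorded as an SAE? | Yes (7.3) | Yes, second sentence | Agreement |

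**One event under each rule.** Take a related SAE of a listed type whose severity goes beyond what the SmPC supports. Rash, muscle weakness and raised transaminases are listed in mild or open-ended terms, so they are suitable examples.

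- *Section 7:* the severity does not fit the SmPC, so the event is unexpected and a SUSAR, reported to the MHRA and main REC in 7 or 15 days.
- *Appendix D alone:* the event is listed, so no MHRA report is required. The outcome is serious, so an SAE form is completed. The list describes it, so it is not a SUSAR.

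**What happens under both rules.** The form reaches the BCTU within 24 hours (7.3). The Chief Investigator reviews all SAEs (7.6). The DMEC sees all SAEs about every 3 months, and any death is passed to it for continuous review (7.3, 7.5). The BCTU's annual report covers all SAEs (7.3).

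**What the wrong label can cost**

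1. The 7- or 15-day report (7.4). The MHRA would first see the event in the annual report, up to about a year later.
2. Unblinding at the Trial Office, which section 6.4 provides for events judged serious, unexpected and related.
3. The BCTU's notice to investigators of SUSARs that compromise safety (7.6).

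**Would a later check correct the label?** Not with certainty. The Chief Investigator assigns expectedness only where no local assessment could be obtained (7.6) and will not overrule the local one (7.4). The route for resolving disagreement is described for SUSARs. No explicit power is given to upgrade an SAE that the site has called expected.

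**Scale.** Up to 64 women randomised equally gives 64 / 2 = 32 exposed. The documents give no expected number of unusually severe listed reactions. As an assumption, apply Appendix D's non-pregnant frequency bands:

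- uncommon term: 32 × 1/1,000 = 0.032 up to 32 × 1/100 = 0.32 cases per term;
- very rare term: below 32 × 1/10,000 = 0.0032 cases per term.

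These counts cover all severities, so cases of unusual severity would be fewer. Whether these rates hold in pre-eclampsia is unknown.

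**The case against.** The strongest reply is that section 7 already takes precedence. It says that the "current expected events for Pravastatin are listed in Appendix D. We will however always use the most recently updated Summary of Product Characteristics (SmPC" is used, section 7.3 sends assessors to the latest SmPC, and Appendix D itself points to section 7. On this view the appendix is an incomplete summary. Much of this stands, and it disposes of three stronger readings.

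- *A reader might infer that a severe reaction could go unreported altogether.* The documents do not support this. Appendix D's own second sentence requires an SAE form, and section 7 then carries the event to the BCTU, the Chief Investigator, the DMEC and the annual report.
- *A reader might infer that a frozen list overrides the SmPC and hides reactions.* The latest SmPC governs under sections 7.1 and 7.3. If the SmPC gains terms, an older list would lead to over-reporting. It would under-report only if terms were removed or narrowed.
- *A reader might think first of liver failure, anaphylaxis or rhabdomyolysis.* These are poor examples, because Appendix D already lists fulminant hepatic necrosis, anaphylaxis, and rhabdomyolysis with acute renal failure.

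On annual reporting, it can fairly be said that the duty lies with the BCTU and that section 7.3 already relieves sites of informing the MHRA. The contradiction on that point is therefore one of wording, with little practical effect while the BCTU follows section 7.3.

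The severity point remains. Appendix D states a complete test, and an investigator who finds the event on the list has no cue to look further. The local label then decides whether the expedited route starts.

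**Conclusion.** The conflict is real and narrow. Appendix D omits the severity criterion that section 7.1 states twice, and its MHRA exemption is worded without the limit to expedited reporting that section 7.3 requires. A related, serious, listed reaction of unusual severity could be labelled expected and so miss expedited reporting, Trial Office unblinding and the notice to investigators. It would not be lost to the trial's safety data.

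This rests on one assumption: that a site applies Appendix D's opening paragraph without going back to section 7. The number of such events is likely to be small and cannot be estimated from the documents. The case for correction is that a stated safety-reporting rule is wrong as written, in a population with little prior exposure. Sample size, endpoints and analysis are unaffected.

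**What to change.** Bring the opening paragraph of Appendix D into line with section 7, for example:

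> Toxicities in the current SmPC do not need expedited reporting to the MHRA unless their severity does not fit that document. An SAE judged related to trial drug is a SUSAR if it is of a type or severity not consistent with the current SmPC. The list below is an aid, and the current SmPC takes precedence. All SAEs, expected or not, remain in the annual report to the MHRA and main REC (section 7.3).

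This replaces the unqualified exemption and the test of whether the list describes the event.

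A neighbouring point can be settled in the same amendment. Section 7.1 also counts recognised complications of pre-eclampsia and of prematurity as expected, whereas its SUSAR definition refers only to the SmPC. The text should say how the two fit together.

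The cost is a few lines in the next amendment, a short note to sites, and possibly an occasional extra expedited report.
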